### Statistical analysis and sample size

Allowing 20% for attrition, and with improvement of ≥ 6 for arm 1 compared to placebo, it is anticipated that 150 participants (75 per arm) should be randomised to achieve a sample size of 60 participants per arm, assuming 80% power, a 1:1 randomisation scheme and a type 1 error of 5% (two-tailed), and a standard deviation of 11.6. The sample size is based on previous work by Hui et al. [13] who determined the minimal clinically important difference in the TSDS to be 5.7 [13]. As such, we have elected to use an improvement of the TSDS of ≥ 6 as a clinically significant change. Stata software (StataCorp. 2013. Stata Statistical Software: Release 13. College Station, TX: StataCorp) was used to estimate the sample size.

The superiority of arm 1 compared to placebo will be tested by comparing the response to each arm after 14 days, relative to baseline.

Descriptive analyses and frequency distributions will be generated from participants’ demographic and clinical characteristics, with all variables explored using graphical methods and summary statistics. For the primary outcome, generalised estimating equations with the appropriate link function will be developed to assess the effect of treatment adjusted for centre. For secondary outcomes, where measurements from individual subjects are recorded several times over the course of the study, change over time in the various secondary outcome measures will be assessed using mixed models, accounting for within-subject correlation and effects due to centre. For all statistical analyses, any influence of potential covariates, for example age, sex, type of cancer and disease severity, will be explored. This study is powered to detect superiority of arm 1 over placebo.

An interim analysis will be performed after 50% participants have completed 14 days of the trial. The analysis will be performed by an independent biostatistician blinded for the treatment allocation and reported to the investigators and the Data Safety Monitoring Board (DSMB). The purpose of the interim analysis is primarily to monitor and ensure safety of participants rather than evidence of such benefit that early stopping of the trial is justified. AEs and SAEs will be stratified by type and severity. The frequency of AEs and SAEs will be compared between treatment groups using chi-square tests and logistic regression if indicated to adjust for any baseline differences between groups. Differences in baseline characteristics are not anticipated, as the randomisation process should ensure that the patient groups are similar at baseline. However, as the numbers at interim analysis will be relatively smaller, it is possible that differences may arise by chance. All baseline characteristics will be assessed and any imbalance addressed in the analysis.

If the interim analysis shows a significant difference, the investigators and DSMB will be un-blinded to the study groups and make any stopping decision on the basis of the nature of any AEs and/or SAEs and ethical grounds, as well as consideration of any statistical differences between the groups. Grounds for stopping on evidence of clear benefit will be considered. The Peto approach will be taken with symmetric stopping boundaries at *p* = 0.001.

A detailed statistical analysis plan will be prepared and ratified by the DSMB. Stata, SAS (SAS® version 9.4 software (SAS Institute Inc., Cary, NC, USA)) or R (R Core Team (2017). R: A language and environment for statistical computing. R Foundation for Statistical Computing, Vienna, Austria. URL https://www.R-project.org/) will be used for analysis and all code recorded for the purposes of ensuring reproducible research.

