### Study participants

Patients who meet the inclusion criteria will have an advanced histologically proven cancer diagnosis (metastatic or locally advanced), be known to and be receiving palliative care at the recruiting centre and have an ESAS Total Symptom Distress Score (TSDS) of ≥ 10/90 for cancer-related symptoms and at least one individual ESAS score ≥ 3/10 [13]. They must have a Performance Status AKPS (Australia-modified Karnofsky Scale score) of ≥ 30/100 [14], be aged ≥ 25 years, have a negative THC urine test at commencement of trial and be able to tolerate oral medications and must be either English-speaking or have an interpreter available.

Female participants must have a negative pregnancy urine test at eligibility (only if of reproductive potential) and agree to avoid pregnancy during the study and 12 weeks following the last dose of the study drug. Males must agree to avoid fathering a child and to not donate sperm during the study and for at least 12 weeks following the last dose of the study drug. Further to this, the Alcohol, Smoking and Substance Involvement Screening Test (ASSIST) will be completed [15]. It is designed to determine whether harmful substances are being used and go undetected or become worse. The assessment is comprised of 8 questions assessing, tobacco, alcohol, cocaine, amphetamine-type stimulants, sedatives, hallucinogens, opiates and ‘other drugs’.

Exclusion criteria include a history of hypersensitivity to any cannabinoid, unstable untreated cardiovascular disease, severe hepatic impairment (total bilirubin ≥ 1.5 times the upper limit of the normal range), aspartate aminotransferase (AST) and alanine aminotransferase (ALT) ≥ 3.0 times the upper limit of the normal range (subjects with liver metastasis may have an AST and ALT of ≥ 5.0 times the upper limit of normal), severe renal impairment (eGFR ≤ 20 mL/min/1.73 m^2^), a history of psychiatric disorders (severe depression or anxiety, personality disorder, psychosis, schizophrenia, first-degree relative with schizophrenia and/or suicidal ideation), cognitive impairment (St Louis University Mental Status examination (SLUMS) ≤ 20/30) [16] and a known substance use disorder (Alcohol, Smoking and Substance Involvement Screening Test (ASSIST) examination scoring > 27) for any substance.

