### Outcomes and assessment tools

The primary outcome is the change from baseline of total ESAS TSDS at day 14.

The ESAS is a 9-item inventory rated on an 11-point scale anchored at 0 (no problem) to 10 (worst problem). It assesses both physical and psychological symptoms, plus general wellbeing. It has been validated in the assessment of symptoms in cancer patients [13].

Secondary outcomes include:
Patient-determined effective dose of THC/CBD formulation, defined as the dose that achieves symptom relief with acceptable side effects.ESAS TSDS at days 7, 21 and 28.Physical and emotional ESAS scores at each time point.
Physical scores will be measured by the Australia-modified Karnofsky Performance Status (AKPS) and Resource Utilisation Groups-Activities of Daily Living Scale (RUG-ADL). The AKPS is a validated variant of the Karnofsky Performance Status. The Australian version can be applied to both in- and outpatients and is sensitive to changes in function over time [14]. The RUG-ADL is an instrument developed for the measurement of nursing dependency. The ADL scale measures patients’ needs for assistance in activities of daily living (eating, bed mobility, transferring and toileting) [17].Individual symptom scores (descriptive analysis only).Oral morphine equivalent (OME), average use at baseline and weekly.Patient Global Impression of Change (PGIC), days 7, 14, 21 and 28.
This is a subjective measure of symptom change completed by the patients themselves [18].Clinical Global Impressions (CGI) Scale, days 7, 14, 21 and 28.
This is a subjective measure of symptom change completed by the investigating clinician [18].The Depression, Anxiety, Stress Scale (DASS-21) score baseline and days 14 and 28.
DASS-21 is a self-reported 21-item scale, 7 questions per sub-item questionnaire measuring depression, anxiety and stress. The DASS-21 will be used for assessment at baseline (day 0) and days 14 and 28 [19].EORTC score QoL baseline and days 14 and 28 [20].This is a QoL measure found valid for use in a wide variety of cancer populations. To reduce patient burden, we will use the 15-question subset commonly used for the palliative care population.NCI common terminology for adverse events V4.03, days 2, 4, 7, 9, 11, 14, 16, 18, 21, 23, 25 and 28 [21]

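### The stated primary analysis of change in TSDS names centre but not baseline TSDS as a covariate, which gives up precision at no saving

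*Protocol article*

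**What the plan says.** All references are to the protocol article.

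- Outcomes and assessment tools: "The primary outcome is the change from baseline of total ESAS TSDS at day 14".
- Statistical analysis and sample size, primary model: "generalised estimating equations with the appropriate link function will be developed to assess the effect of treatment adjusted for centre". Centre is the only adjustment named.
- Same section, other covariates, for all analyses: "any influence of potential covariates, for example age, sex, type of cancer and disease severity, will be explored". The list is open, but baseline TSDS is not on it.
- Same section, interim-analysis text: "All baseline characteristics will be assessed and any imbalance addressed in the analysis". This follows the comparison of adverse events between groups and names no covariate.
- Study participants: patients must "have an ESAS Total Symptom Distress Score (TSDS) of ≥ 10/90 for cancer-related symptoms", so no one enters without a TSDS.
- Planning values: "with improvement of ≥ 6 for arm 1 compared to placebo", "and a standard deviation of 11.6", "a type 1 error of 5% (two-tailed", 80% power, 60 evaluable per arm and 150 randomised after 20% attrition. The text does not say whether 11.6 is the SD of change or of a single TSDS.

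**The concern.** A change score fixes the coefficient on baseline at 1. If rho is below 1 and the variances are similar at the two visits, the best linear prediction of day-14 TSDS uses a smaller coefficient, so full subtraction takes off too much. Two things follow. The treatment contrast carries avoidable noise. And if the arms happen to differ at baseline, the arm that starts worse will tend to show the larger fall for reasons unrelated to treatment. As described, randomisation is blocked within centre only, so the design does not balance baseline TSDS.

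At stake is efficiency in a trial sized at its 80% target with almost nothing to spare, in a population where extra participants are hard to recruit and the covariate is already collected.

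**Working it through.** **Inputs from the article:** difference 6, SD 11.6, two-sided 5%, 80% power, 1:1 allocation, 20% attrition.

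**Assumptions:** rho from 0.3 to 0.8; equal variances at baseline and day 14; a linear relation; two-sample noncentral t with 118 degrees of freedom (the few lost to centre and baseline are ignored).

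**1. The plan's own figure.** The normal approximation gives n per arm = 2 × (11.6 × (1.96 + 0.842) / 6)² = 58.7, so 59. With the noncentral t, power is 79.6% at 59 and 80.2% at 60, so 60 per arm. Then 60 / 0.8 = 75 per arm, 150 in total. The stated size reproduces.

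**2. Variance ratio.** With common single-visit variance s²:

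- change score: 2s²(1 − rho)
- baseline-adjusted: s²(1 − rho²)
- ratio, adjusted to change: (1 + rho) / 2

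The ratio is below 1 for any rho below 1. The variance saved is (1 − rho) / 2: 35% at rho 0.3, 25% at 0.5, 15% at 0.7 and 10% at 0.8.

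**3. If 11.6 is the SD of change.** The change score has 80.2% power and a 95% CI half-width of 1.98 × 11.6 × √(2/60) = 4.19. The adjusted SD is 11.6 × √((1 + rho)/2).

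| rho | adjusted SD | power at 60 per arm | CI half-width |
|---|---|---|---|
| 0.3 | 9.35 | 93.6% | 3.38 |
| 0.4 | 9.71 | 91.9% | 3.51 |
| 0.5 | 10.05 | 90.1% | 3.63 |
| 0.6 | 10.38 | 88.1% | 3.75 |
| 0.7 | 10.69 | 86.2% | 3.87 |
| 0.8 | 11.00 | 84.2% | 3.98 |

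**4. If 11.6 is the SD of a single TSDS.** The change SD is 11.6 × √(2(1 − rho)); the adjusted SD is 11.6 × √(1 − rho²).

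| rho | change SD | power, change | adjusted SD | power, adjusted |
|---|---|---|---|---|
| 0.3 | 13.73 | 66.1% | 11.07 | 83.8% |
| 0.4 | 12.71 | 72.7% | 10.63 | 86.6% |
| 0.5 | 11.60 | 80.2% | 10.05 | 90.1% |
| 0.6 | 10.38 | 88.1% | 9.28 | 94.0% |
| 0.7 | 8.99 | 95.2% | 8.28 | 97.6% |
| 0.8 | 7.34 | 99.3% | 6.96 | 99.7% |

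**5. Residual error from chance imbalance.** If the arms differ by D at baseline, the change-score contrast is shifted by −(1 − rho)D. Taking 11.6 as the SD of change, the single-visit SD is 11.6 / √(2(1 − rho)), and one standard error of the baseline difference is that SD × √(2/60).

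- rho 0.3: SD 9.80, standard error 1.79, shift 0.7 × 1.79 = 1.25 points
- rho 0.5: SD 11.60, standard error 2.12, shift 0.5 × 2.12 = 1.06 points
- rho 0.7: SD 14.98, standard error 2.73, shift 0.3 × 2.73 = 0.82 points

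These compare with a target difference of 6.

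**The case against.** The strongest reply is that the article names centre without saying that centre is the only covariate, leaves the covariate list open, and defers to a detailed statistical analysis plan that is not shown. That plan may already include baseline TSDS. Nor does the text say how baseline enters the estimating equations. This stands as a limit on the point: the article does not exclude baseline adjustment. It does, however, fix a change outcome and a stated adjustment. Exploring covariates is not prespecifying one, and the promise to deal with imbalance sits in the interim text and depends on what is observed.

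For the secondary outcomes, the planned mixed models of change over time may already carry baseline as a response, so the request there is conditional.

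A reader might also infer more than the document supports:

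- **That the analysis is biased or the sample size wrong.** The change-score contrast is unbiased over randomisation, and 60 per arm reproduces.
- **That baseline imbalance goes uncorrected.** The change score does remove the baseline difference; it removes too much. Only the (1 − rho) remainder is left.
- **That the trial is underpowered.** This holds only if 11.6 is a single-visit SD and rho is below 0.5. At 0.5 and above on that reading, the change score meets the target.
- **That the TSDS entry threshold makes matters worse.** Under a linear relation, truncating baseline leaves slope and residual variance alone and shrinks baseline variance, so the gain from adjustment falls. With an untruncated rho of 0.5, the variance ratio moves from 0.75 to 0.83 (cut 1 SD below the mean) or 0.89 (cut at the mean). Regression to the mean from selection affects both arms alike.

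**Conclusion.** The point holds as a loss of efficiency, not as an invalid analysis. The primary model as stated does not use baseline TSDS as a covariate, and adding it cannot reduce large-sample precision. How much it helps depends on a correlation and on a reading of 11.6 that the article does not supply. If 11.6 is the SD of change, the gain is roughly 10 to 13 power points at rho 0.3 to 0.5, falling to about 4 at rho 0.8. If it is a single-visit SD, the gain runs from about 18 points at rho 0.3 to 2 or 3 at rho 0.7. All these figures rest on equal variances at the two visits. The direction of the gain is secure; calling it substantial is justified only at the lower correlations.

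**What to change.** Before unblinding, and before the interim comparison if that is still possible, state the primary model in the protocol or analysis plan as day-14 TSDS (or its change) on treatment, continuous baseline TSDS and centre. The treatment coefficient is the same whether the response is the day-14 score or the change, once baseline is a covariate. Account for baseline in the same way for each secondary outcome that has a baseline value, unless the mixed model already does so. State whether 11.6 is the SD of change or of a single TSDS.

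The cost is a few lines of text. It needs no new data and no more participants, and the sample size need not change.

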**Table Taba:** 

Measure	Source	Collected by
General medical information	Clinical record	Medical officer
General demographic data	Clinical record	Study nurse
Pathology results—blood	Pathology report	Pathology
Pathology results—urine	Clinical record	Study nurse
Vital signs	CRF/clinical record	Study nurse
Concurrent medications/OME	Clinical record	Study nurse
Study trial data—questionnaires—ASSIST, SLUMS, EORTC QLQ-C15-PAL	CRF	Patient, study nurse, medical officer
Study trial data—ESAS, AKPS, RUG-ADL, PGIC, CGI-S/I, DASS-21	CRF	Patient, study nurse, medical officer
Side effects—safety	CRF, clinical record	Study nurse, medical officer

All data collected will be kept in a patient file (identified by ID number only). All data will be stored in a locked filing cabinet. At completion of the study, all CRFs will be collated and archived. Electronic files will be password protected and held within a locked office. All patient files will be reconciled and stored along with all study materials, both hard copy and electronic, consistent with the regulations of the hospital regarding the retention and disposal of patient records.

The trial will be conducted with permission and in accordance with Queensland Health regulations on the use of medical cannabis and subject to approval and monitoring by each clinical site’s HREC [4, 22]. An independent DSMB to include a statistician, clinical pharmacologist, palliative care specialist and consumers will be formed and will meet regularly, with primary responsibility for monitoring adverse and serious adverse events. All AE’s and SAE’s will be reviewed at a minimum of 6 monthly intervals, or more frequently if needed.

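### The interim rule makes the DSMB's knowledge of which arm is which follow from a significant test, and gives no route to it after a non-significant one, although the look is mainly for safety and the test is weak

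*Protocol article*

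**What the plan says.** All of this is in the Protocol article. The section Statistical analysis and sample size sets the timing: "An interim analysis will be performed after 50% participants have completed 14 days of the trial". It gives the aim: "The purpose of the interim analysis is primarily to monitor and ensure safety of participants". The analysis is "performed by an independent biostatistician blinded for the treatment allocation and reported to the investigators and the Data Safety Monitoring Board". AEs and SAEs are broken down by type and severity, and the test is named: "The frequency of AEs and SAEs will be compared between treatment groups using chi-square tests and logistic regression if indicated".

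The rule on arm identity follows: "If the interim analysis shows a significant difference, the investigators and DSMB will be un-blinded to the study groups and make any stopping decision". That decision is to rest on the nature of the events, on ethics and on the statistical differences. The only interim threshold stated is the one for stopping, "The Peto approach will be taken with symmetric stopping boundaries" at p = 0.001. The level that counts as significant for unblinding is not given.

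The section Data collection and management describes the DSMB as the body "with primary responsibility for monitoring adverse and serious adverse events" and has events reviewed at least every six months. It does not say whether those reviews are by arm, coded or with the key. The Study design section lists who stays blind until the end of the trial. The DSMB is not on that list.

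**The concern.** The order of steps is the wrong way round for a safety look. Whether an excess of events matters depends on which arm it is in and what the events are. Under the stated rule the board learns which arm it is in after a test has reached significance. If the test does not, the text gives the board no way to find out.

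The article lists confusion, paranoia and psychosis among the known cannabinoid events. A board looking at groups A and B can see that such events cluster in one of them. It cannot tell whether that group is on THC/CBD or on placebo, where the same excess would point to disease or chance. It therefore cannot weigh the nature of the events as the rule itself asks. A few grave events can matter clinically without ever reaching significance in a sample of this size.

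This is a rule that the article states, and it works badly when followed. It is not a detail left to the analysis plan.

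**Working it through.** **1. The plan's own figure.** The article gives no power or event rate for the interim safety test. Its only sample-size figure is for the primary outcome, and it reproduces. With a difference of 6, SD 11.6, two-sided 5% and 80% power, n = 2(1.960 + 0.842)² × 11.6² / 6² = 58.7 per arm. The t-based version gives 59.65, so 60. Then 60 / (1 − 0.20) = 75 per arm, or 150 in total.

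**2. Numbers at the interim.** Half of 150 is 75, or 37 and 38 per arm. If half of the 120 evaluable participants is meant, it is 60, or 30 per arm.

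**3. Power of one comparison.** The event rates below are assumptions, because the article gives none. Each row is a doubling on active treatment. The normal approximation is

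power = Φ{ [ |p₂ − p₁|√n − z√(2p̄(1 − p̄)) ] / √( p₁(1 − p₁) + p₂(1 − p₂) ) }.

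For 10% v 20%, n = 37 and z = 1.96: 0.10 × √37 = 0.608; 1.96 × √(2 × 0.15 × 0.85) = 0.990; the denominator is √(0.09 + 0.16) = 0.5. So power = Φ(−0.382 / 0.5) = Φ(−0.763) = 0.22.

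Exact enumeration of the two binomials with the uncorrected chi-square test gives the values below. The ranges depend on which arm has 38.

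| Placebo v active (assumed) | Power at 5%, 37 and 38 | Missed at 5% | Power at 5%, 30 and 30 | Power at 0.001, 37 and 38 |
|---|---|---|---|---|
| 5% v 10% | 0.116-0.130 | 87-88% | 0.106 | 0.001 or less |
| 10% v 20% | 0.223-0.235 | 77-78% | 0.194 | 0.010-0.012 |
| 15% v 30% | 0.346-0.355 | 65% | 0.281 | 0.034 |
| 20% v 40% | 0.472-0.485 | 51-53% | 0.392 | 0.071-0.074 |
| 30% v 60% | 0.783-0.790 | 21-22% | 0.663 | 0.253-0.258 |

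If the trigger for unblinding is the stated p = 0.001, the miss is about 74% or more in every row (1 − 0.258 = 0.742). With 30 per arm at 5%, the miss at 10% v 20% rises to 81%.

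**4. An illustration.** Suppose 8 of 37 have an event on active and 4 of 38 on placebo. The risk difference is 0.216 − 0.105 = 0.111. With pooled risk 12/75 = 0.16, z = 0.111 / √(0.16 × 0.84 × (1/37 + 1/38)) = 1.31, so p = 0.19. The 95% interval is 0.111 ± 1.96 × 0.084, or about −5 to 28 percentage points. The test is not significant, so the stated rule opens no route to arm identity, yet the data are compatible with a large harm.

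**5. What cannot be computed.** The gate is not one test. The article compares AEs as well as SAEs, by type and severity, and does not say which of these must be significant or at what level. Several tests at the same level would open the gate more often than one. The table describes a single event type and not the gate as a whole.

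**The case against.** The strongest reply is that the article is narrower than its critics may make it.

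- A reader might infer that the board can learn arm identity only if the test is significant. The text says if, and does not bar the board from asking for the key. The board is absent from the Study design blinding list, and the format of the six-monthly reviews is not stated. They might be unblinded under a charter that is not shown. This stands as a caution on wording. It does not remove the point: a board that will be un-blinded must be blind beforehand, and no other route for group-level identity is given. The emergency code break in Study design does not serve group-level review.
- A reader might infer that a harmful excess would pass unexamined. The documents do not support that. The comparison by type and severity is reported to the DSMB whatever its result, so on the natural reading the board sees coded groups. What it lacks is the direction. Nor does the article say that a non-significant test counts as evidence of safety.
- A reader might attach one headline figure, such as a doubling missed three times in four. That needs a placebo risk near 11% and a 5% trigger, and the article gives neither.
- The content of closed reports is usually a charter matter, and masking a DSMB is a choice that some boards make. That is fair. Making the board's access depend on significance is nevertheless a stated rule, and a charter that followed it would inherit the problem.

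**Conclusion.** The point holds in this form. The article makes group-level unblinding of the DSMB, and the stopping judgement on the nature of events, follow from a significant difference at a look that is mainly for safety. It states no route to arm identity otherwise. The board is blind to direction, not to the existence of an imbalance.

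The size depends on assumptions. For a single event type at two-sided 5% with 37 to 38 per arm, the chance of missing a doubling runs from 87-88% at 5% v 10% to 21-22% at 30% v 60%. It is higher with 30 per arm, and about 74% or more throughout if the trigger is p = 0.001. These figures show that non-significance is weak reassurance at low and moderate event rates. They are not the miss rate of the whole gate. The rule should be changed, and the change does not depend on which event rate is right.

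**What to change.** Remove the significance condition as it applies to the DSMB. State that:

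- at the interim and at each periodic review, the DSMB receives a closed report of AEs and SAEs by coded arm, with risk differences and 95% confidence intervals;
- the DSMB may obtain the key on request at any time, whatever the p-value;
- a non-significant test is not taken as evidence of safety.

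The cost is wording in the protocol and the DSMB charter, plus preparation of the closed report. No participants or visits are added. There are two downsides. DSMB members may lose their masking. Someone independent of the investigators must also hold the key, whereas Study design now places the un-blinded schedule with an investigator not directly involved in randomising patients.

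The same sentence also un-blinds the investigators, while Study design keeps them blind until trial completion. Those two statements should be reconciled in the same edit.

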### Study design

This study is a pragmatic multicentre, randomised, placebo-controlled, two-arm parallel trial of escalating doses of oral THC/CBD 10 mg/10 mg/mL oral solution. There is a 2-week patient-determined titration phase, using escalating doses of a 1:1 THC/CBD combination or placebo, to reach a dose that achieves symptom relief with tolerable side effects. This is followed by a further 2-week assessment period on the stable dose determined in collaboration with clinicians.

Eligible patients will be randomly assigned in equal numbers to one of the two study arms. Randomisation schedules will be developed for each site using random number tables, computer generated at an independent centre. Treatment for each patient will be allocated according to a permuted block randomisation schedule held by the central registry. Block randomisation within each centre will ensure even allocation to each arm in each site. The pharmacy will be notified of a participant, and a completed script with the participant’s study ID number will be given to the site pharmacy. The pharmacist will randomise the participant according to the schedule and dispense the medication in a labelled bottle. The participant ID, allocation number, date of request, preparation and dispensing will be recorded in a log maintained by the site pharmacist for each randomisation.

All participants, caregivers, investigators and clinical staff will remain blind to study assignment until trial completion. The code will only be broken in cases of a clinical emergency. An investigator not directly involved in the randomisation of patients will keep an un-blinded copy of the randomisation schedule and will be contacted in the event of the need to un-blind. All study drugs and placebo will be in oil solution form and identical in appearance. All oil solutions will be matched for taste, colour and bottle size to preserve the blinding irrespective of the contents; each participant will receive the oil solution in a prepacked bottle labelled with their individual trial participation ID number and consecutively numbered according to the randomisation scale.

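### The interim rule gives investigators the between-group results and may un-blind them mid-trial, contradicting the commitment to keep them blind until completion

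*Protocol article*

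**What the plan says.** Two sections of the protocol article set rules on investigator blinding.

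- **Study design.** "All participants, caregivers, investigators and clinical staff will remain blind to study assignment until trial completion". One exception is given: "The code will only be broken in cases of a clinical emergency".
- **Statistical analysis and sample size, on timing.** "An interim analysis will be performed after 50% participants have completed 14 days of the trial".
- **Same section, on who sees the results.** The analysis is "performed by an independent biostatistician blinded for the treatment allocation and reported to the investigators and the Data Safety Monitoring Board (DSMB"). It compares adverse events (AEs) and serious adverse events between groups by chi-square tests, with logistic regression if needed.
- **Same section, on un-blinding.** If a significant difference is found, "the investigators and DSMB will be un-blinded to the study groups and make any stopping decision". Investigators and DSMB then decide on stopping together. Stopping for clear benefit may be considered, using Peto boundaries at p = 0.001.

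The level of 0.001 is given for stopping. No level, and no outcome, is given for the difference that leads to un-blinding.

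**The concern.** A statistical comparison at the halfway point is not a clinical emergency, and it comes before trial completion. An investigator who follows the interim rule therefore breaks the blinding rule.

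The stake is the data still to be collected if the trial continues after un-blinding:

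- Research staff help define each participant's dose before the day-14 primary outcome (Intervention).
- The investigating clinician rates the CGI, which the protocol calls subjective (Outcomes and assessment tools).
- Outcomes are recorded at medical review visits (Assessments). Nurses and medical officers are listed among those who collect ESAS, PGIC, CGI and side-effect data (Data collection and management).
- The primary outcome is a total of 0 to 10 symptom ratings, and the Discussion cites high placebo response as the reason a placebo is essential.

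Part of the exposure does not need the trigger. The investigators receive the group comparison in any event. Even under coded labels, an excess of cannabinoid-type AEs in one group could suggest which group is active.

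**Working it through.** **1. The two rules side by side.**

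| Question | Study design | Interim rule |
|---|---|---|
| Until when are investigators blind? | Trial completion | Possibly only until the 50% analysis |
| What permits un-blinding? | Clinical emergency only | A significant difference, not defined |
| Who sees interim group results? | Not addressed | Investigators and DSMB |

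The first two rows cannot both be followed.

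**2. The plan's own figures.** Difference 6, SD 11.6, two-sided 5%, 80% power:

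n = 2 × (1.960 + 0.842)² × 11.6² / 6² ≈ 58.7, so 59 per arm by the normal formula. The t-based calculation gives 60 (power 0.802). Then 60 / 0.80 = 75 per arm, 150 in total. The stated size reproduces. One look at 0.001 with a final test at 0.05 gives an overall type 1 error of 0.0502, so alpha spending is not the problem.

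**3. How much data could be affected.** If half of 150 have passed day 14, at most about 75 participants have day-14 data still to come. If the interim instead waits for 75 completers and the planned 20% attrition falls before day 14, then 75 / 0.80 ≈ 94 are already randomised and about 56 remain to be enrolled.

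**4. How likely the trigger is under each reading of its level.**

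From the protocol: about 75 participants at the interim (38 v 37), chi-square tests, and the 12 AE types named as known and common. Assumed: independent AEs, a 15% rate for each, and a true difference of 40% v 15% where one exists.

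Exact enumeration of the chi-square test gives, per AE:

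- at 0.05: false-positive rate 0.0513, power 0.695
- at 0.001: false-positive rate 0.00050, power 0.177

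The chance of at least one significant AE is:

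- no true difference: 1 − (1 − size)¹²
- one AE differs: 1 − (1 − power)(1 − size)¹¹
- three AEs differ: 1 − (1 − power)³(1 − size)⁹

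| Scenario | p < 0.05 | p < 0.001 |
|---|---|---|
| No true difference | 47% | 0.6% |
| One AE at 40% v 15% | 83% | 18% |
| Three AEs at 40% v 15% | 98% | 45% |

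The null figure at 0.05 also depends on the assumed event rate: about 7% at a 2% rate, 37% at 5% and 47% at 15%.

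**The case against.** Much can be said in the plan's favour.

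- **The trigger may be strict.** A reader might infer that any AE with p < 0.05 un-blinds the investigators, so that un-blinding is likely. The document does not say so. The only level given for the interim is 0.001, in the same paragraph, and under it a false trigger is rare. The plan also promises a detailed analysis plan, which could define the level. This stands: the probability of un-blinding cannot be fixed from the text.
- **The AE model is rough.** Nausea and vomiting, or anxiety and paranoia, plausibly occur together, so independence is only an approximation. This stands too.
- **Un-blinding to groups may mean labels only.** The schedule is held by the central registry, pharmacists allocate, and bottles match. The interim biostatistician is blinded, so the first report is presumably by coded group. Individual codes may never be released. This limits the damage, but comparative knowledge would still be with the investigators, and a mid-trial un-blinding is still not a clinical emergency.
- **Participants stay blind.** Any effect on their symptom ratings is indirect, through staff contact and dose discussions. Bias also requires the trial to continue. A reader might conclude that drug effect and bias could not be separated at all, which goes too far.
- **The people may differ.** A reader might assume that those who receive the report are the same people who consent, titrate and rate. The protocol gives consent to trained team members and dose agreement to research staff, and does not say which investigators receive the report. The overlap is partly inference, except that the CGI rater is described as the investigating clinician.
- **The emergency copy.** The plan also says that "An investigator not directly involved in the randomisation of patients will keep an un-blinded copy of the randomisation schedule". A reader might count this as a second breach, but no section says this person treats or rates participants. Where that copy is held is an optional matter and does not carry the point.

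None of this removes the contradiction.

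**Conclusion.** Wrong as written. The interim rule conflicts with the blinding rule on two points: how long investigators stay blind and what may end their blinding. It also sends comparative results to the investigators whether or not the trigger is met.

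The contradiction rests on the text alone and needs no assumption. The consequence is conditional. If the trial continues after un-blinding, bias in data from at most about half the participants could not be reliably excluded. Its size cannot be computed from the document. The chance of reaching that point ranges from under 1% to over 80% for zero or one true AE difference, depending on a threshold the protocol does not state and on assumed AE rates. The text therefore does not support saying that un-blinding will probably occur.

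**What to change.** In the interim paragraph of Statistical analysis and sample size:

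1. Send group-wise interim results only from the independent biostatistician to the DSMB.
2. Allow only the DSMB to be un-blinded. The investigators receive its recommendation without group data and stay blind to completion, as Study design already requires.
3. State the outcome and the significance level that trigger DSMB un-blinding, and say whether this level is the same as the 0.001 stopping boundary.

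The cost is wording in the protocol and the DSMB charter. The plan already provides for an independent biostatistician and an independent DSMB with its own statistician, so no new body, data or participants are needed. The change should be in force before the interim analysis, because investigators cannot be re-blinded afterwards.
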